## Abstract

**Introduction:**

Friedreich Ataxia (FRDA) is an autosomal recessive neurodegenerative disorder that causes gait and limb ataxia, dysarthria, and impaired vibratory sense, with cardiomyopathy being the predominant cause of death. There is no approved therapy, which results in the use of symptomatic treatments and the chronic support of physiotherapy. Dimethyl fumarate (DMF) is a fumaric acid ester used for the treatment of psoriasis and Multiple Sclerosis (MS). It induces Nrf2 *in vitro* and *in vivo*, and it increases frataxin in FRDA patient lymphoblasts, in mouse models, and in MS treated patients.

**Methods:**

The aim of our study is to investigate if DMF can increase the expression of the *FXN* gene and frataxin protein and ameliorate *in-vivo* detectable measures of mitochondrial dysfunction in FRDA. The study is composed of a screening visit and two sequential 12-week phases: a core phase and an extension phase. During the first phase (core), patients will be randomly assigned to either the DMF or a placebo group in a 1:1 ratio. During the first week, patients will receive a total daily dose of 240 mg of DMF or placebo; from the second week of treatment, the dose will be increased to two 120 mg tablets BID for a total daily dose of 480 mg. During the second phase (extension), all patients will be treated with DMF. EudraCT number 2021-006274-23.

**Endpoints:**

The primary endpoint will be a change in *FXN* gene expression level after 12 weeks of treatment. Secondary endpoints will be frataxin protein level, **c**ardiopulmonary exercise test outputs, echocardiographic measures, Nrf2 pathway and mitochondrial biogenesis gene expression, safety, clinical scales, and quality of life scales.

**Conclusions:**

This is the first study aimed at exploring the ability of DMF, an already available treatment for MS and psoriasis, to correct the biological deficits of FRDA and potentially improve mitochondrial respiration *in-vivo*.

## Introduction

### Background

Friedreich Ataxia (FRDA), an autosomal recessive neurodegenerative disorder, is the most common hereditary ataxia among persons of European ancestry (Harding, 1981). The disease is characterized by gait and limb ataxia, dysarthria, usually absent tendon reflexes, bilateral Babinski sign, and an impaired vibratory sense. Cardiomyopathy is the predominant cause of death (Filla et al., 2000).

The molecular defect is a trinucleotide GAA expansion in the first intron of the *FXN* gene (Campuzano et al., 1996) that encodes frataxin, a 210 amino acid mitochondrial protein. Compared to controls, FXN/mRNA is reduced to 20% in patients and to 53% in carriers (Saccà et al., 2011). In patients, frataxin protein is 36% of the level seen in controls and shows an inverse correlation with the size of the GAA repeat in the shorter allele (GAA1). Although the exact physiological function of frataxin is not known, it may have a role in iron–sulfur (Fe–S) cluster biogenesis, iron binding/storage, and scavenging against reactive oxygen species (ROS) (Bulteau et al., 2004).

All cells have an intrinsic protective mechanism from ROS that is controlled through the transcription factor Nrf2 that binds to the antioxidant response element (ARE) in the regulatory regions of target genes (Nguyen et al., 2003). Nrf2 is normally sequestered in the cytoplasm through interaction with Keap1, which results in constitutive ubiquitination and proteasomal degradation. Excessive ROS results in the modification of Keap1 such that Nrf2 is no longer constitutively degraded (Linker et al., 2011). A reduction in antioxidant defenses has been reported in fibroblasts from FRDA patients, highlighted by a deficiency in Nrf2 activation (Paupe et al., 2009), suggesting that FXN deficiency may cause lower Nrf2 activation and decreased mitochondrial antioxidant protection (Hayashi and Cortopassi, 2016).

Therapeutic strategies in FRDA include increasing frataxin protein and/or FXN/mRNA levels and replacing frataxin function (i.e., antioxidation or iron chelation). Antioxidants such as idebenone, a short chain quinone analog of CoQ10, are ineffective on the clinical course of the disease (Lynch et al., 2010). Erythropoietin (EPO) is a glycoprotein that acts as a main regulator for erythropoiesis. EPO increases frataxin levels in cultured human lymphocytes from FRDA patients. A phase IIb multicenter, randomized, placebo-controlled clinical trial showed no effect of Epoetin alfa on exercise capacity and on peak oxygen uptake (VO_2_max) at the cardiopulmonary exercise test (CPET) in FRDA patients (Saccà et al., 2016). Nicotinamide appears to be effective in increasing FXN/mRNA and frataxin protein levels when used at doses much higher than recommended, but several adverse events (AEs) occurred during the phase I trial of nicotinamide, and affected virtually all treated patients (nausea, lightheadedness, vomiting, and headache) (Libri et al., 2014). This will probably affect drug adherence and limit the long- term use of the drug. Considering that FRDA is a chronic condition, this may be a serious limitation to nicotinamide. Omaveloxolone is an activator of Nrf2 and restores mitochondrial function *ex vivo* in fibroblasts from people with FRDA, but there is no evidence that it can increase the levels of *FXN* gene expression and frataxin protein. Omaveloxolone significantly improved neurological function measured with the modified Friedreich's Ataxia Rating Scale (mFARS) compared to placebo and was generally safe and well tolerated (Lynch et al., 2021). The U.S. Food and Drug Administration (FDA) has recently approved Omaveloxolone as a treatment for FRDA.

Although several trials have been performed with FRDA patients, no effective treatment is available in Europe, and clinical practice consists of preventing the development of cardiomyopathy, and in the symptomatic management of the disease.

### Study rationale

A screening protocol for repurposed drugs that rescue frataxin-dependent defects in FRDA fibroblasts resulted in the identification of dimethyl fumarate (DMF) (Sahdeo et al., 2014), which dose-dependently increases frataxin in FRDA patient lymphoblasts.

DMF induces Nrf2 *in vitro* and *in vivo*, modifying cysteine residues in Keap1 (Linker et al., 2011). DMF also regulates HDAC expression and increases acetylation of H3.3 and H2A (Kalinin et al., 2013). Nrf2-binding sites exist in the *FXN* gene, as demonstrated by Chromatin Immuno- Precipitation (ChIP) experiments (Sahdeo et al., 2014), which represents one of DMF's modes of FXN induction.

Also, in the FRDA mouse models YG8 and KIKO with a dose range 3–10 mg/kg, DMF caused a dose-dependent increase in frataxin protein in the cerebellum and in multiple other tissues (Jasoliya et al., 2019). We recently found that DMF induces mitochondrial biogenesis and function in human fibroblasts and increases mitochondrial copy number, the mitochondrial biogenesis factor TFAM, 10 mitochondrial transcripts, and maximal mitochondrial O_2_ consumption rate (Jasoliya et al., 2019). NCF2 and PDLIM1 were also recently validated in human FRDA lymphoblast lines as markers of DMF treatment (Hayashi et al., 2017).

We performed an exploratory study to limit expenses and risks related to a straight phase II trial with DMF in patients with FRDA. We enrolled multiple sclerosis (MS) patients, for which a decision to start a therapy with DMF (*n* = 14) had already been taken as part of normal clinical practice, at the standard dose of 240 mg BID. We added to this study a parallel group of patients that started a treatment with fingolimod (*n* = 12), a recently approved oral treatment for MS, that served as a control group. We also enrolled twelve healthy controls. Baseline levels of FXN/mRNA in PBMCs were similar between controls and MS patients (*p* = 0.818). After 3 months of treatment, FXN/mRNA expression increased by 85.1% in the DMF group and 13.7% in the fingolimod group (relative increase in DMF +71.4%; *p* = 0.011). DMF also caused a 70% increase in mitochondrial copy number in PBMCs and an >100% increase in mitochondrial complex subunit expression of mt-ND6 (complex 1), mt-CYB (complex 3), mt-CO_2_ (complex 4) and mt-ATP6 (complex 5). The increase in these four transcripts could result in an *in-vivo* stimulation of mitochondrial biogenesis and improvement of oxidative phosphorylation, known to be impaired in FRDA patients (Hayashi et al., 2017).

Since MS patients showed comparable basal levels of FXN/mRNA to healthy controls, it is possible that DMF can increase FXN/ mRNA levels in healthy individuals as well as in patients with MS.

Based on the previous points, the aim of our study is to further investigate the role of DMF in FRDA and to demonstrate if DMF is able to correct the biological deficits of FRDA. The study will contribute to the understanding of the ability *in-vivo* of DMF, at currently approved doses for MS and psoriasis, to increase the expression of the *FXN* gene and to increase frataxin protein.

We propose a double-blind, placebo-controlled, randomized, phase II clinical trial to test the effect of DMF on FXN transcription in FRDA patients. The secondary objectives of the study will be the effect of DMF on frataxin protein, the nrf2 pathway, and mitochondrial biogenesis, safety and tolerability, and clinical aspects of the disease.

We hypothesize that DMF is superior to placebo in its ability to increase FXN/mRNA.

### The drug—dimethyl fumarate

DMF is a fumaric acid ester that has been used for the treatment of psoriasis (Rostami-Yazdi et al., 2010) due to its suppressive actions on pro-inflammatory T-cell activation and to shift T-cell polarity from Th1 to Th2 (Bovenschen et al., 2010). Recently, DMF received approval from the EMA for the treatment of psoriasis based on the positive results of the BRIDGE trial (Mrowietz et al., 2017). DMF has also been considered for the treatment of MS (Gold et al., 2012) and was approved for the treatment of relapsing remitting MS.

After oral intake, DMF is rapidly hydrolyzed by esterases to its active circulating metabolite monomethyl fumarate (MMF). DMF is currently administered due to its lower incidence of gastrointestinal side effects compared to MMF (Litjens et al., 2004). MMF's bioavailability is decreased by concurrent food ingestion, though it remains bioavailable. MMF is the most bioactive metabolite (Litjens et al., 2004) and typically reaches peak serum concentrations around 20 μM. MMF is eliminated mainly through breathing; only small amounts of intact MMF are excreted through urine or feces. There is no evidence for a cytochrome P450-dependent metabolism in the liver, thus few drug interactions would be expected. MMF's half-life *in vivo* is around 12 h. The safety profile of DMF (trade name: Skilarence) is well-known and adverse events of special interest that have been considered for Skilarence are (EMA/412737/2017, 2017) leukocytopenia and lymphopenia, flushing, gastrointestinal disorders, hepatic injury, malignancies, renal injuries and proteinuria, and serious and opportunistic infections. The reported incidence of leukocytopenia is 13.3%, and lymphopenia is 10.0%, with very few patients (<1%) experiencing severe enough lymphopenia (<0.5/L) to lead to discontinuation. Flushing has an incidence of up to 20.8% of patients, is more frequent during the first weeks of treatment, and tends to resolve during long-term administration of DMF. Gastrointestinal disorders were reported in 62.7% of patients receiving DMF. They usually resolved after the first few months of treatment. The proportion of patients with an increase in hepatic enzymes is 7.5% and all are usually mild/moderate intensity. There is no evidence that long-term treatment with DMF is associated with an increased risk of malignancies. The proportion of patients reporting renal injury/proteinuria is low (<3%). Several of these cases of renal toxicity occurred with doses of fumaric acid esters that are much higher than the dose recommended for DMF in psoriasis/MS. In all of these cases, the renal function returned to normal after stopping treatment. The number of infections during DMF treatment was very low (<5%). All infections resolved by the end of the studies or during the 2-month follow-up period. No relation was found between leukopenia/lymphopenia and infections.

## Methods and analysis

### Trial design and intervention

This will be a single-center trial with only one center activated at the AOU Federico II University Hospital. The study is composed of a screening visit and two sequential 12-week phases: a core phase and an extension phase (Figures 1, 2). During the core phase, patients will be randomly assigned to either a DMF or placebo group. During the extension phase, all patients will be treated with DMF.

**Figure 1 F1:**
[figure not shown]
Drug disposition for the core and extension phase. DMF, dimethyl fumarate.

**Figure 2 F2:**
[figure not shown]
Study visit plan and procedures. V1, visit 1; V2, visit 2; V3, visit 3; V4, visit 4; V5, visit 5; V6, visit 6; V7, visit 7; V8, visit 8; V9, visit 9; V10, visit 10; ECG, electrocardiogram; Con Meds, concomitant medications; SARA, Scale for the Rating and Assessment of Ataxia; m-FARS, modified Friedreich Ataxia Rating Scale; FXN/mRNA, *FXN* gene mRNA measurement; PRT, PATA rate test; 9HPT, 9 hole pegboard test; ADL/IADL, activities of daily living/Instrumental activities of daily living; EQ-5D, European quality of life scale; CPET, cardiopulmonary exercise test; EcoCG, echocardiography.

The use of placebo is based on several factors. On one side, there is a need for a more accurate evaluation on the biochemical effect on FXN/mRNA and frataxin that can show fluctuations over time. For this reason, an increase of FXN/mRNA in an open-label trial could be erroneously attributed to treatment. The second reason is that secondary endpoints (CPET, Clinical scales, etc.) can show a clear placebo effect once patients take part in a clinical trial. There is no known risk of being in the placebo group as there is no treatment available for FRDA.

The study will begin with a screening visit where patients will sign their informed consent (Figure 2). We will then assess inclusion and exclusion criteria (Table 1). Patients fulfilling all inclusion and none of the exclusion criteria will undergo endpoint measurement and will enter the core phase of the study.

**Table 1 T1:** Inclusion and exclusion criteria.

**Inclusion criteria**
1. Molecular diagnosis of Friedreich Ataxia with a homozygous GAA expansion 2. Age ≥12 years 3. Body weight ≥30 Kg 4. Patients able to read and sign the informed consent form
**Exclusion criteria**
5. Treatment with DMF in the previous 12 months 6. Treatment with Idebenone, coenzyme Q10, or any other vitamin supplements in the previous 30 days 7. Patients in treatment with any other not allowed drug 8. Any Cardiac and/or Renal and/or Hepatic disease judged as clinically significant by the investigator (any abnormal and clinically non-significant cardiac disease associated with Friedreich Ataxia is not an exclusion criteria) 9. Any clinically significant ECG abnormalities that may interfere with the study 10. Any abnormal and clinically significant laboratory exams at screening visit that may interfere with the trial 11. Any acute disease that could interfere with the study, as judged by the investigator 12. Patient positive to the Human Immunodeficiency Virus (HIV) or Hepatitis B or C test 13. Patients with a positive history of neoplasia, with the only exception of a completely excided basal cell carcinoma 14. Positive history of alcohol or drug abuse in the past 2 years, except for medical use of cannabis 15. Hypersensitivity to DMF or any other component of the study drug 16. Patients not able to comply with the study 17. For female patients (Sexually inactive, hysterectomized, sterilized, or menopause patients are excluded from the following criteria): a) Pregnancy, or b) Breastfeeding, or c) Inadequate contraception

GAA, guanine-adenine-adenine triplet; DMF, dimethyl fumarate; ECG, electrocardiogram.

After entering the core phase, patients will be randomized to receive either DMF or placebo in a 1:1 ratio. Randomization will start with the retrieval of randomization lists that will be generated by the private CRO (FullCRO) involved in the study. Randomization will be in blocks of four and will be stratified based on GAA triplet repeat expansion (group I < 635; group II ≥635). For safety reasons, the treating physician will be able to break the code of a single patient and be informed of the allocation between active treatment and placebo. This will be followed by the immediate discontinuation of the patient.

For the first week of the core phase, patients randomized to the treatment group will receive one 120 mg tablet BID, for a total daily dose of 240 mg. Starting from the second week of treatment, the dose will be increased to two 120 mg tablets BID for a total daily dose of 480 mg (Figure 1). Rationale for the selected treatment dose is derived from the approved dose of DMF for Multiple Sclerosis and Psoriasis patients and the previously reported effect of DMF 240 mg BID in Multiple Sclerosis patients (Jasoliya et al., 2019). The placebo group will receive identical placebo tablets. Patients will refer to the study center for endpoint re-assessment and drug accountability procedures after 1, 4, 8, and 12 weeks. Patients completing the 12-week core phase will roll-over in a 12-week extension phase. Please see Figure 2.

During the extension phase, to maintain blindness to treatment allocation, at week 13, patients receiving DMF in the core phase will continue with DMF 480 md/day in the form of two 120 mg DMF tablets BID. Patients receiving placebo in the core phase will receive one tablet of DMF 120 mg BID and one placebo tablet BID. From week 14 to 24, all patients will receive two 120 mg DMF tablets BID. Patients will again be visited after 1, 4, and 12 weeks after entering in the extension phase. A detailed description of the study activities is shown in Table 2.

**Table 2 T2:** Visit schedule.

**Phase**		**Core Phase**					**Extension phase**				**EOS**
**Visit**	**1**	**2**	**3**	**4**	**5**	**6**	**7**	**8**	**9**	**10**	
**Activities and evaluations**	**Screening (**−**1 to** −**2 weeks)**	**Baseline**	**Week 1–day 7 (**±**1 day)**	**Week 4–day 28 (**±**4 days)**	**Week 8–day 56 (**±**1 week)**	**Week 12–day 84 (**±**1 week)**	**Week 13–day 91 (**±**1 day)**	**Week 16–day 112 (**±**4 days)**	**Week 20–day 140 (**±**1 week)**	**Week 24–day 168 (**±**1 week)**	**Study interruption**
Informed consent	X										
Inclusion/exclusion criteria	X	X									
Demographics	X										
Diagnosis	X										
Past and actual medical history	X										
Randomization		X									
Physical examination and vital signs	X	X	X	X	X	X	X	X	X	X	X
Concomitant therapies	X	X	X	X	X	X	X	X	X	X	X
ECG	X					X				X	X
Neurological examination	X	X				X				X	X
SARA	X	X				X				X	X
m-FARS	X	X				X				X	X
PATA rate Test		X				X				X	X
9HPT		X				X				X	X
CPET		X				X				X	X
ECOCG		X				X				X	X
EQ-5D		X				X				X	X
ADL/IADL		X				X				X	X
Drug administration/accountability		X	X	X	X	X	X	X	X	X	X
Adverse events		X	X	X	X	X	X	X	X	X	X
Routine biochemistry	X	X	X	X	X	X	X	X	X	X	X
Hematology	X	X	X	X	X	X	X	X	X	X	X
Urine examination	X	X	X	X	X	X	X	X	X	X	X
Blood sampling for protein/RNA	X	X	X	X	X	X	X	X	X	X	X
Pregnancy test	X			X	X	X		X	X	X	X

ECG, electrocardiogram; SARA, Scale for the Rating and Assessment of Ataxia; m-FARS, modified Friedreich Ataxia Rating Scale; 9HPT, 9 hole pegboard test; ADL/IADL, activities of daily living/instrumental activities of daily living; EQ-5D, European quality of life scale; CPET, cardiopulmonary exercise test; EcoCG, echocardiography.

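### Exclusion criterion 17 places its exemption before the whole list, so some pregnant or breastfeeding women fall under no named exclusion; separately, no pregnancy test is marked at the visit where eligibility is re-checked

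*Protocol article*

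**What the plan says.** **Eligibility rule.** Table 1 of the protocol article, exclusion criterion 17, applies to female patients. It carries a parenthesis ahead of its three lettered items: "Sexually inactive, hysterectomized, sterilized, or menopause patients are excluded from the following criteria): a) Pregnancy, or b) Breastfeeding", with inadequate contraception as item c).

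**What the rule controls.** The section on trial design and intervention makes Table 1 the gate to treatment: "Patients fulfilling all inclusion and none of the exclusion criteria will undergo endpoint measurement and will enter the core phase of the study".

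**When it is applied.** In the Table 2 visit schedule, the eligibility row is marked at visit 1 (screening, 1 to 2 weeks before baseline) and visit 2 (baseline): "Inclusion/exclusion criteria X X". Randomisation is marked at visit 2 only, and drug administration is first marked there too. The row labelled "Pregnancy test" is marked at visits 1, 4, 5, 6, 8, 9 and 10 and at study interruption. It is blank at visits 2, 3 and 7. Visit 4 is at day 28 ± 4 days.

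**The concern.** An exclusion criterion is applied literally by the site and checked literally by the monitor. The section on good clinical practice itself names adherence to the eligibility criteria as a specific hazard of this study. An exemption that switches off the wrong items therefore matters even if everyone can guess what was meant.

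Here the exemption stands before the list and refers to criteria in the plural, so it governs all three items. Two of them, pregnancy and breastfeeding, are current states of the patient, and not every exempt group is free of them. At stake is the protection of participants in a trial that enrols from age 12.

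The visit schedule raises a second, smaller question: when criterion 17 is re-applied at baseline, the latest scheduled pregnancy result is already one to two weeks old.

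**Working it through.** No power, alpha or rate enters this point, and the plan states no figure to reproduce. The check is a reading of the criterion, followed by a short calculation from the visit windows.

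**Step 1. Apply the exemption to each item.** For each exempt group, ask whether the state named in the item can still be present.

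| Exempt group | a) Pregnancy | b) Breastfeeding | c) Inadequate contraception |
|---|---|---|---|
| Currently sexually inactive | possible: the pregnancy may already exist | possible | exemption coherent |
| Sterilised | unlikely | possible | exemption coherent |
| Hysterectomised | practically excluded | not ruled out by the operation | exemption coherent |
| Menopausal | practically excluded | not relied on here | exemption coherent |

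The clear failures are the sexually inactive woman who is pregnant or breastfeeding, and the sterilised woman who is breastfeeding. Read as written, neither meets any part of criterion 17.

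**Step 2. Look for another rule that catches them.** No other text in the article excludes pregnancy or breastfeeding. The nearest candidates in Table 1 are these:

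- Criterion 10 concerns clinically significant abnormal laboratory results at screening. It names neither state, depends on judgement, and cannot identify breastfeeding.
- Criterion 11 concerns acute disease that could interfere, as judged by the investigator. It names neither state.
- Criterion 16 concerns inability to comply with the study. It names neither state.

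The visit 1 pregnancy test supplies information on pregnancy but not on breastfeeding. For an exempt woman, a positive result has no named criterion to act on.

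**Step 3. Interval between pregnancy tests around first dosing.** Take baseline (visit 2) as day 0.

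- Visit 1 test: 7 to 14 days before day 0.
- Visit 4 test: day 28 − 4 = 24 to day 28 + 4 = 32.
- Shortest gap: 7 + 24 = 31 days.
- Longest gap: 14 + 32 = 46 days.
- Part of the gap after drug is first given at visit 2: 24 to 32 days, on DMF or placebo.

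The eligibility re-check, randomisation and first drug administration all fall inside this gap.

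**The case against.** The strongest reply is that this is a loosely worded attempt to describe women of childbearing potential. For hysterectomised and menopausal women the exemption from a) does no harm, and for sterilised women almost none. Table 2 marks a pregnancy test at visit 1 with no group exempted, so a pregnancy detectable then would be known before randomisation. Criteria 10 and 11 leave some discretion, and a site is unlikely to randomise knowingly a woman it knows to be pregnant. The trial plans 40 patients, so few could be affected.

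Much of this stands, and it narrows the point to the cases in step 1. It does not remove it: none of these safeguards reaches breastfeeding, and discretion is no substitute for a named exclusion. Nor is this a matter of an article condensing a fuller protocol, since the criterion is printed with both its list and its exemption.

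On the visit schedule the reply is stronger. Nothing in the article promises a pregnancy test at visit 2, and re-checking eligibility need not mean repeating each screening procedure. The ECG is likewise marked at visit 1 and not at visit 2, although criterion 9 rests on it. That part is therefore a request for reconciliation, not an error.

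A reader might infer more, in three ways that the document does not support:

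- **That the blank cell at visit 2 allows pregnant patients to be randomised.** It does not. A pregnant woman outside the exempt groups remains excluded by 17a whether or not she is tested that day. Only the parenthesis removes an exclusion.
- **That a patient found pregnant at visit 4 would be lost from the core phase.** The withdrawal criteria under the study population heading are four laboratory thresholds plus physician discretion. Pregnancy is not mentioned.
- **That up to 32 days means 32 days of DMF.** Allocation is 1:1, so on average half of such patients would be on placebo.

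**Conclusion.** Criterion 17 is wrong as written. Followed literally, it leaves a sexually inactive woman who is pregnant or breastfeeding, and a sterilised woman who is breastfeeding, under no named exclusion. It is probably a drafting slip in which the exemption was meant for contraception alone, but the article does not say so, and Table 1 is the operative gate.

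The visit 2 point is separate and lesser: 31 to 46 days between scheduled pregnancy tests, spanning the eligibility re-check and first drug administration, after a screening test 1 to 2 weeks before baseline. The intervals assume that visits fall within the printed windows and that dosing starts at visit 2.

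The number of women in the affected groups is not given. That it is likely small is a judgement from the planned total of 40 patients and the narrowness of the cases. The sample size, power, type I error and primary analysis are unaffected. The case for acting rests on participant protection and on having a criterion that can be monitored as worded.

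**What to change.** 1. **Table 1, criterion 17.** Move the parenthesis so that it qualifies item c) alone. Items a) and b) then apply to all female patients, and the four groups stay exempt from the contraception requirement. For example: a) pregnancy; b) breastfeeding; c) inadequate contraception (not applicable to sexually inactive, hysterectomised, sterilised or menopausal patients). This costs one line and should not affect recruitment noticeably.

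2. **Table 2.** Reconcile the eligibility check at visit 2 with the pregnancy-test row, either by stating which result supports 17a at baseline or by aligning the two rows. The choice is the sponsor's; no testing rule is proposed here. The minimum cost is a footnote or one table cell.

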#### Secondary endpoints

The secondary clinical objectives are to examine changes on the cardiopulmonary exercise outputs (VO_2_max, anaerobic threshold, and peak workload) and echocardiographic measures; and to evaluate differences in the Scale for the Rating and assessment of Ataxia (SARA), modified Friedreich Ataxia Rating Scale (m-FARS), 9-hole pegboard test (9HPT), EQ-5D, Activities of Daily Living (ADL)/Instrumental Activities of Daily Living Scale (IADL), and number and distribution of serious and non-serious adverse events between DMF and placebo.

The secondary laboratory objectives are to determine the effect of DMF on *FXN* and frataxin protein considering the change from baseline to week 12 and week 24 and at week 1 of the core phase, and at week 1 of the extension phase for those patients transitioning from placebo to DMF, compared to other time-points obtained after a DMF dose of 240 mg BID. Other secondary endpoints explore the effect of DMF on Nrf2 pathway genes (*NFE2L2, NQO1, HMOX1, PDLIM1*, and *NCF2*), on mitochondrial biogenesis genes (mt-ND6, mtCYB, mt-CO_2_, and mt-ATP6), and on mtDNA/nDNA.

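### Table 2 ties visit 7 to study day 91 although visit 6 can fall on days 77-91, so if extension drug starts at visit 6 the switchers' week-1 FXN mRNA sample can follow about 1 to 15 days of DMF instead of 6-8

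*Protocol article*

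**What the plan says.** Under Trial design and intervention, the end of the core phase leads straight into the extension: "Patients completing the 12-week core phase will roll-over in a 12-week extension phase". The next paragraph times the extension visits from that entry: "Patients will again be visited after 1, 4, and 12 weeks after entering in the extension phase". It sets the switchers' dosing by study week. At week 13, "Patients receiving placebo in the core phase will receive one tablet of DMF 120 mg BID and one placebo tablet BID". After that, "From week 14 to 24, all patients will receive two 120 mg DMF tablets BID".

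Table 2 uses study days throughout. Visit 3 is day 7 ±1 day, visit 6 is day 84 ±1 week, visit 7 is day 91 ±1 day, visit 8 is day 112 ±4 days and visit 10 is day 168 ±1 week. Visit 6 stands under the core phase. The rows "Drug administration/accountability" and "Blood sampling for protein/RNA" are marked at both visit 6 and visit 7.

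The Secondary endpoints section gives the visit 7 sample a purpose. FXN is to be examined "at week 1 of the extension phase for those patients transitioning from placebo to DMF", and the result is to be set against samples taken on the full dose of 240 mg twice daily.

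**The concern.** The visit 7 sample is meant to show the response after about one week on the lower dose, to be set against samples taken on the full dose. It is informative only if time on drug is controlled. The ±1 day window, the same as at visit 3, suggests that the sponsor wanted that control. A narrow window around a fixed study day does not provide it when the event that starts the clock can itself move by a week either way. A site that follows Table 2 to the letter could then take the switchers' samples after very different lengths of treatment, all of them within protocol.

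**Working it through.** **Inputs** (Table 2)

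- Visit 6: 84 ± 7, so days 77 to 91 (15 permitted days).
- Visit 7: 91 ± 1, so days 90 to 92 (3 permitted days).
- Target exposure: 7 ± 1 = 6-8 days, as at core visit 3, and in line with a visit one week after entry.
- Assumption: the first extension dose is taken at the actual visit 6.

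**The plan's own figure.** 84 + 7 = 91, so the nominal dates in text and table agree. The mismatch comes only from the windows.

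**Exposure at visit 7** = visit 7 day − visit 6 day.

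| Visit 6 day | Days of DMF at visit 7 (day 90, 91, 92) |
|---|---|
| 77 | 13, 14, 15 |
| 81 | 9, 10, 11 |
| 82 | 8, 9, 10 |
| 83 | 7, 8, 9 |
| 84 | 6, 7, 8 |
| 85 | 5, 6, 7 |
| 86 | 4, 5, 6 |
| 87 | 3, 4, 5 |
| 91 | −1, 0, 1 |

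Only visit 6 on day 84 gives 6-8 days for every permitted visit 7 day. Visit 6 on days 82-86 allows 6-8 days for at least one visit 7 day. For days 77-81 and 87-91, which are 5 + 5 = 10 of the 15 permitted days, no compliant visit 7 does.

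**All permitted pairs:** 15 × 3 = 45.

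- 6-8 days: 1 + 2 + 3 + 2 + 1 = 9 pairs (20%), from visit 6 on days 82 to 86.
- 9-15 days: (5 × 3) + 2 + 1 = 18 pairs (40%), from visit 6 on days 77-81, 82 and 83.
- 5 days or fewer: 1 + 2 + (5 × 3) = 18 pairs (40%), from visit 6 on days 85, 86 and 87-91. Two of these put both visits on the same day (90/90 and 91/91), and one puts visit 7 before visit 6 (visit 6 on day 91, visit 7 on day 90).

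Leaving out those three, the range is 1 to 15 days. These are counts of what the windows allow. They do not forecast how visits will fall.

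**Dose at the sample.** If the low-dose step lasts 7 days from the actual first dose, samples at 9-15 days come after the rise to 480 mg/day. If the step follows study weeks, as the text words it, an early visit 6 mainly lengthens the time at 240 mg/day, and a visit 6 near day 91 leaves almost no low-dose week. Time on drug is uncontrolled either way; dose is mixed as well under some rules but not all.

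**After re-anchoring to visit 6**

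- Visit 7 = visit 6 + 7 ± 1: exposure is 6-8 days for everyone; study days 77 + 6 = 83 to 91 + 8 = 99.
- Visit 8 = visit 6 + 28 ± 4: study days 77 + 24 = 101 to 91 + 32 = 123. Exposure is 24-32 days, against 108 − 91 = 17 to 116 − 77 = 39 under the present table.
- Visit 10 left on day 168 ± 7: exposure 161 − 91 = 70 to 175 − 77 = 98 days, as now.

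**The case against.** The text already names the right anchor, and the table agrees with it nominally. A site that schedules from entry obtains 6-8 days, so one can say that only the table's wording is at fault. That stands in part: the intention is probably sound. But the table is the schedule against which visits are judged, its windows are printed in full, and nothing visible tells a site to shift visit 7 when visit 6 moves.

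Figures 1 and 2 cover drug disposition and the visit plan and could not be seen. They may state the start day. This stands, and it makes the finding conditional.

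Two stronger readings are tempting, and the document supports neither.

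- A reader might infer that the late visit 7 samples are taken on the very dose with which they are to be compared. That requires the step-up to be counted from the actual first dose. The text ties it to study weeks, and drug handling is also marked at visit 7, so the step may follow that visit.
- A reader might infer that the switch is fixed at study day 84, so that a visit 6 on days 85-91 would draw the week-12 placebo sample after DMF has begun and touch the primary endpoint. That is strained. Visit 6 belongs to the core phase in Table 2, has drug handling marked, and roll-over follows completion of the core phase.

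It is also fair that the consequence is small and that actual days on drug could be recovered from visit dates and accountability records. Recovery would describe the spread in exposure but would not remove it.

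**Conclusion.** The point holds as a minor inconsistency with a practical effect. With extension drug started at the actual visit 6, the printed windows allow about 1 to 15 days of DMF before a sample that should follow 6-8, and 10 of the 15 permitted visit 6 days rule out 6-8 altogether. Whether the longer exposures include days at 480 mg/day cannot be settled from the text.

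The reach is one secondary FXN mRNA time point in about 20 switchers (half of the 40 planned, before drop-out). The core week-1 sample is not involved. The Frataxin measurement section does not list a protein assay at this visit, and the Statistical analysis section treats the analysis that adds switchers as descriptive only. The primary week-12 comparison is not affected. The conclusion rests on the drug starting at visit 6 and on the unseen figures not stating otherwise.

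**What to change.** - State that extension drug starts at the actual visit 6, after the week-12 blood draw.
- In Table 2, set visit 7 = visit 6 + 7 ±1 days and visit 8 = visit 6 + 28 ±4 days.
- Run the switchers' 240 mg/day step from that start until visit 7, with 480 mg/day only after the visit 7 sample. This replaces the study-week wording. A fixed 7-day step would also serve, provided that the increase still waits for the sample when visit 7 falls on day 8.
- Leave visits 9 and 10 on study days 140 ±7 and 168 ±7, so that the week-24 change from baseline keeps its timing. Reword the sentence on visits at 1, 4 and 12 weeks to match.

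The cost is wording in Table 2 and a few sentences, with no extra visits, samples or patients. The tablets given at visit 6 must last to the latest permitted visit 7, 8 days later. The downside is a wider spread in study time: visit 7 on days 83-99 (now 90-92) and visit 8 on days 101-123 (now 108-116). Time on DMF at visit 10 stays at 70-98 days. Anchoring visit 10 to visit 6 as well would narrow this to 77-91 days but spread visit 10 over study days 154-182, so it is not proposed.
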